**Figure 2 F2:**
[figure not shown]
Indication of acupoints location of the acupuncture prescription in this study. The name, English code and location of each acupoint is in accordance with WHO Standard Acupuncture Point Locations in the Western Pacific Region. Retaining needles for 60 mins. Lifting, thrusting, twisting and/or rotating the needles once every 20 mins with intermittent stimulation for maintaining the deqi sensation for twice. EX-HN, Extrachannel points; GB, Gallbladder Meridian; GV, Governor Vessel; LI, Large Intestine Meridian; LR, Liver Meridian; ST, Stomach Meridian.

### Cointerventions

Patients will be advised not to undergo any additional treatments for their migraine, and ibuprofen (300 mg each capsule with sustained release) will be recommended for management of severe pain, according to the evidence-based clinical practice guidelines (Scottish Intercollegiate Guidelines Network, 2018) (18). In intolerance or unresponsive to ibuprofen cases, other tolerable and responsive non-steroidal anti-inflammatory drugs (NSAIDs) could be used. The patients will be asked to record the name and dosage of any co-interventions they use during this clinical trial in a headache diary.

### Patient Safety

Routine examination of basic parameters, such as liver and renal function, as well as blood, urine, and feces will be performed in all patients prior to and after acupuncture treatment. Moreover, electrocardiography tests will be conducted prior to treatment, while any side effects following acupuncture will be descriptively recorded in the Case Report Form (CRF). Severe adverse events will also be monitored, managed, followed up, and recorded as previously described. These will be reported to the Ethics Committee within 24 h of occurrence.

### Outcome Measures

All MwoA patients will be asked to keep a headache diary during the whole 24-week observation period. The following endpoints will be assessed: (1) primary endpoint, namely number of migraine days and attacks; (2) secondary endpoints, namely response rates, severity of headache pain, quality of life, anxiety/depression of the patients, NSAIDs use, and adverse events; (3) other endpoints will include needle sensation evaluations and the patient's expectations for the acupuncturist. To ensure reliability of the results, all outcome data will be independently collected by trained assessors, and the acupuncturist will not be present during evaluation. Details on measurement of outcomes and the time of data collection are described below and in Table 1.

#### Primary Outcome Measurement

The primary outcomes will comprise changes in the mean number of migraine days and the frequency of migraine attacks per 4 weeks cycle, compared to those at baseline.

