**ASSESSMENTS:**									
The headache diary									
Number of days with migraine	**×**	**×**		**×**		**×**	**×**	**×**	**×**
Frequency of migraine attacks	**×**	**×**		**×**		**×**	**×**	**×**	**×**
Positive response rate				**×**		**×**	**×**	**×**	**×**
Mean VAS score		**×**		**×**		**×**	**×**	**×**	**×**
SAS score		**×**		**×**		**×**	**×**	**×**	**×**
SDS score		**×**		**×**		**×**	**×**	**×**	**×**
The use of NSAIDs									
MIDAS		**×**		**×**		**×**	**×**	**×**	**×**
MSQ		**×**		**×**		**×**	**×**	**×**	**×**
AES		**×**							
MASS									

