**PARTICIPANTS SAFETY:**									
Laboratory test		**×**				**×**			
Adverse events									

*This study includes 4-week baseline period, 8-week treatment period and 12-week follow-up period for each migraine patient*.

*AES, acupuncture expectations evaluation scale; MASS, Massachusetts General Hospital acupuncture sensation scale; MIDAS, Migraine Disability Assessment Scale; MSQ, Migraine-Specific Quality-of-Life Questionnaire; NSAIDs, nonsteroidal anti-inflammatory drugs; SAS, self-rating anxiety scale; SDS, self-rating depression scale; VAS, visual analog scale; Laboratory test: including routine examination of blood, urine and stool, blood biochemical test (including liver and kidney function), and electrocardiogram examination*.

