### Sample Size Estimation

There is no available reference of clinical trials regarding the effect of patients' expectations of different acupuncturists on acupuncture-based migraine treatment so far. Our clinical experience and results from preliminary experiments indicate that the reduction number of migraine days was 3.9 ± 2.49 in the senior acupuncturist group, compared to 2.7 ± 3.45 days in the junior acupuncturist group at weeks 4–8 of treatment. PASS software version 15 was used to calculate the sample size, based on 80% power to detect a significant difference (α = 0.05, two sided), and with an excepted dropout rate of ~20%, target enrollment was set at 156 patients (78 patients in each group).

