### Statistical Analysis

Intention-to-treat analyses will be performed where possible, with subgroup and sensitivity analyses performed, where necessary, to detect possible heterogeneity of the results. All data will be statistically analyzed using SPSS version 26.0 (SPSS Inc., Chicago, IL, USA). Two-tailed analyses will be conducted, with the level of statistical significance defined set at *P* < 0.05. Data from normally distributed continuous variables will be expressed as means with their respective standard deviations (SD), unless otherwise specified, whereas categorical variables will be presented as numbers and percentages. Distribution of continuous variables will first be analyzed using the Shapiro-Wilk test and normal probability plot. Next, we will perform a Student's *t*-test to determine differences between groups for normally distributed data. The nonparametric test will be used for skewed data, or on data with heterogeneity of variance or unknown distribution. Comparisons in response rates and incidence rate of adverse events between groups will be performed by Chi-square or Fisher's exact tests.

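### Two primary outcomes per 4-week cycle, with no primary cycle and no rule on whether one or both must be significant, while the sample size rests on migraine days at weeks 4–8 only

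*Protocol article*

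**What the plan says.** All references are to the protocol article.

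- **Primary Outcome Measurement** gives the definition: "The primary outcomes will comprise changes in the mean number of migraine days and the frequency of migraine attacks per 4 weeks cycle", each compared with baseline. The abstract says the same.
- **Outcome Measures:** both variables appear under a singular label, "primary endpoint, namely number of migraine days and attacks". They are not ranked, and no success rule is given.
- **Table 1:** the rows "Number of days with migraine" and "Frequency of migraine attacks" are both marked at weeks 4, 8, 12, 16 and 20 after baseline. This agrees with the table footnote, "8-week treatment period and 12-week follow-up period for each migraine patient": two treatment cycles and three follow-up cycles.
- **Sample Size Estimation:** the planning figures are for the reduction in migraine days only, "at weeks 4–8 of treatment". Attack frequency and the other four cycles are not sized.
- **Statistical Analysis:** "Two-tailed analyses will be conducted, with the level of statistical significance defined set at" P < 0.05. For the comparison of groups, "we will perform a Student's" t-test, or a nonparametric test where its conditions fail. The section gives no ordering of the primary outcomes and no way of combining the cycles.
- **Hypotheses:** the second hypothesis expects a moderately better effect with the senior acupuncturist. It attaches no outcome or time to that expectation.

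**The concern.** A primary definition should tell the reader which single result, or which stated combination of results, decides the trial. This one gives two variables repeated over every cycle, while the sample size assumes one variable in one window. The two sections do not describe the same primary comparison.

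Two things are at stake. First, if either outcome at any cycle may carry the conclusion, the chance of a false claim exceeds the stated 5%. Second, the deciding outcome and cycle could be chosen after the results are seen. Patients and acupuncturists are unblinded and the diary is kept by the patient, so a clear prior commitment matters more than usual.

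**Working it through.** **Inputs from the document.** Two primary outcomes; five post-baseline 4-week cycles (Table 1); two-sided 0.05; reductions of 3.9 (SD 2.49) and 2.7 (SD 3.45) migraine days; 80% power; about 20% dropout; 78 per group.

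**Assumed, because the document gives no values.** Correlation 0.5–0.9 between the two outcomes and 0.3–0.9 between cycles.

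**1. The plan's own sample size.** Difference = 3.9 − 2.7 = 1.2. Sum of variances = 2.49² + 3.45² = 6.200 + 11.903 = 18.103. Evaluable n per group = (1.960 + 0.842)² × 18.103 / 1.2² = 98.7, so 99. With 20% dropout, 99 / 0.8 = 123.75, so 124 per group and 248 in total. The stated 78 per group (156) is not reproduced. That is a separate matter, but it sets the power figures in step 5.

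**2. Number of comparisons on the widest reading.** 2 outcomes × 5 cycles = 10. The count comes from Table 1; the protocol does not state it.

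**3. Chance of at least one false positive, either outcome at any cycle.** If independent: 1 − 0.95¹⁰ = 40.1%. With correlation, ten normal test statistics were simulated (400,000 draws). All pairs of cycles had the same correlation, and the correlation across both outcome and cycle was the product of the two. A false positive is any |z| > 1.96.

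| Between cycles | Between outcomes | At least one false positive |
|---|---|---|
| 0.3 | 0.5 | 35.1% |
| 0.5 | 0.5 | 31.1% |
| 0.7 | 0.7 | 23.6% |
| 0.9 | 0.9 | 13.9% |

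Counting only false positives that favour one named group, the range is about 7–18%, against a nominal 2.5%.

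**4. Narrower readings.**
- Either outcome at one cycle: 1 − 0.95² = 9.75% if independent; 9.1% at correlation 0.5 and 7.0% at 0.9.
- One outcome at any of five cycles: 20.8%, 18.3%, 15.0% and 10.1% at cycle correlations 0.3, 0.5, 0.7 and 0.9.
- Both outcomes significant in the same direction at one cycle, when neither truly differs: 0.9% at correlation 0.5 and 3.0% at 0.9. Error does not exceed 5%; the cost is power.

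**5. Power for migraine days under the planning effect.** Standard error = √(18.103 / n); Welch noncentral t. The 62 per group is 78 × 0.8 = 62.4, rounded down.

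| n per group | SE | 1.2 / SE | Power at 0.05 | Power at 0.025 |
|---|---|---|---|---|
| 78 | 0.482 | 2.491 | 69.6% | 59.0% |
| 62 | 0.540 | 2.221 | 59.5% | 48.2% |

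**The case against.** The strongest reply is that the text nowhere says the trial succeeds on any of ten tests. A reader might infer this from Table 1, but Table 1 is a schedule of data collection. It marks VAS, SAS, SDS, MIDAS and MSQ at the same five post-baseline visits. No success rule is stated at all. The singular label in Outcome Measures is compatible with both outcomes being required, and the primary outcome wording could mean an average, or a rate per 4 weeks, over the period. The weeks 4–8 window in the sample size section suggests a narrower intention. A multiplicity procedure is also something an article may leave to the full protocol or the analysis plan. This all stands, so the ten-test reading can be described only as permitted, and the absence of a multiplicity method in this article is not itself the fault.

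The reply does not remove the mismatch. The article does state its primary definition, and that definition covers two variables per cycle, without adopting the window used for sizing. An analysis plan that chose one variable and one cycle would be changing the definition, not filling in detail. The alternative readings do not resolve it either. An average over cycles leaves two unadjusted primaries and departs from the sized window. A both-must-win rule controls error, but it is not stated and was not sized.

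The choice of migraine days over attack frequency could be called preference. Its justification is that this is the comparison for which the plan gives planning figures.

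**Conclusion.** The point holds as an ambiguity in the primary definition and a mismatch with the sample size. The article does not fix which outcome, which cycle, or how many successes decide the trial.

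The size depends on the reading. It is about 14–35% for either outcome at any cycle (40% only under independence, which is implausible for repeated diary counts in the same patients), about 7–9% for either outcome at one cycle, and no inflation if both must be significant at one cycle. The percentages rest on assumed correlations and equal correlation between cycles. The documents do not support saying that the trial will declare success on any of ten tests, or that its type I error is a particular figure; they support saying that nothing in the stated definition prevents it. This should be settled before any unblinded analysis.

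**What to change.** Before any unblinded analysis, amend the protocol and the registry entry as follows:

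1. **Single primary:** change from baseline in migraine days in the second 4-week treatment cycle, compared between groups at two-sided 0.05. State that weeks 4–8 in the sample size section means this window, that is, the four weeks ending at the week-8 visit.
2. **Next in order:** change in attack frequency in the same window, tested only if the primary is significant.
3. **All other cycles, for both outcomes:** secondary, reported with confidence intervals and no confirmatory claim.

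**Cost.** This order needs no split of alpha and adds no patients for multiplicity. Attack frequency loses standalone primary status. Recruitment began in March 2021, so the change must be documented as a dated amendment, with a statement that it was made without sight of outcome data by group.

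**If both outcomes stay primary,** name the one cycle and state the success rule: Holm, or both must be significant. Neither is a mere change of wording. At Holm's first step (0.025), power for migraine days is about 59% with 78 per group and 48% with 62, against about 70% and 60% at 0.05. Holm's overall power for migraine days is somewhat higher, because the threshold returns to 0.05 if attack frequency succeeds first. A both-must-win rule cannot have more power than the migraine-days test alone, so at most about 70% or 60%. Its exact power cannot be computed, because the article gives no planning figures for attack frequency.

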### Secondary Outcome Measurement

#### Positive Response Rate

A positive responder is a patient that exhibits at least 50% reduction in migraine days or frequency (19). The proportion of positive responders will be counted every 4 weeks, from baseline to endpoints.

#### Headache Severity

The intensity of headache will be assessed using the mean visual analog scale (VAS), which comprises a range of 0–10 points (20). This will be done from baseline to endpoints.

#### Emotional Status

Anxiety and depression symptoms will be assessed using the *Zung* Self-rating Anxiety Scale (*Zung* SAS) (21) and *Zung* Self-rating Depression Scale (*Zung* SDS) (22), respectively. Both scales have a 20-item self-reporting questionnaire, which are scored on a 4-point Likert scale (range 0–4 points) according to the frequency of symptoms in the past 4 weeks. A high SAS or SDS score (≥50) indicates severe anxiety or depression, respectively.

#### Quality of Life

We will employ the Migraine-Specific Quality-of-life Questionnaire (MSQ) (23), a validated and widely accepted tool that measures health-related quality of life (24). The MSQ measures a person's functional level, with higher scores implying better function. The Migraine Disability Assessment Scale (MIDAS) (25), a five-item questionnaire developed to measure headache-related disability that reveals the impact of migraine on daily functioning over the past three months, will also be used. MIDAS total scores range from 0–27 points, while MIDAS grades are defined as follows: I (0–5), II (6–10), III (11–20), and IV (>20), of which grade IV indicates the highest disability. Changes in MSQ and MIDAS scores will be measured every 4 weeks, from baseline to endpoints.

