### Study Design

This will be a single-center, two parallel-group, randomized clinical trial. A total of 156 MwoA patients will be recruited, then randomly allocated to either senior or junior acupuncturist groups, at a ratio of 1:1. The study will be conducted for a period of 24 weeks for each patient, comprising the following phases: baseline (4 weeks), treatment (8 weeks), and follow-up (12 weeks). AES will be used to evaluate patients' expectations for acupuncture efficacy delivered by either a junior or senior acupuncturist before randomization. A summary of the study protocol is presented using a flowchart (Figure 1) while the schedule is outlined in Table 1. This protocol is reported in accordance with the guidelines of the Consolidated Standards of Reporting Trials (CONSORT) (14) and Standards for Reporting Interventions in Clinical Trials of Acupuncture (STRICTA) (15).

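### MIDAS has a three-month recall but is analysed as change every 4 weeks, so the week-4 and week-8 scores still contain pre-treatment time and would understate any effect at those visits

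*Protocol article*

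**What the plan says.** Under Quality of Life, the protocol article introduces MIDAS as a five-item questionnaire that "reveals the impact of migraine on daily functioning over the past three months". The same paragraph then fixes the measure and the interval: "Changes in MSQ and MIDAS scores will be measured every 4 weeks, from baseline to endpoints".

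Read against its column headings, the MIDAS row of Table 1 has six marks: weeks 0, 4, 8, 12, 16 and 20. Study Design gives a 4-week baseline, an 8-week treatment phase and a 12-week follow-up. Treatment therefore runs from week 0 to week 8, and follow-up ends at week 20.

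Quality of life is a secondary endpoint. Outcome Measures lists "secondary endpoints, namely response rates, severity of headache pain, quality of life" among others.

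For the anxiety and depression scales, the Emotional Status section states a recall that matches the visit interval: items are scored "according to the frequency of symptoms in the past 4 weeks". No such 4-week adaptation is mentioned for MIDAS.

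**The concern.** A scale that looks back three months cannot give a clean reading of what happened since week 0 until about three months after week 0. At week 4 most of the period the patient reports on comes before the first needle; at week 8, the end of treatment, part of it still does. Those weeks were already scored at week 0, so they add nothing to a change score. They also precede randomisation, so they cannot carry a difference between the senior and junior arms.

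The trial sets out to quantify the size of an effect that its own hypotheses call moderate. If MIDAS change at weeks 4 and 8 is reported beside MSQ and the diary outcomes as though it covered the same interval, there are two risks. A small or absent MIDAS difference at end of treatment could be read as evidence of no effect on disability. A MIDAS improvement that grows from week 4 to week 12 could be read as delayed benefit when part of the growth comes from the window sliding forward.

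**Working it through.** The plan gives no figure of its own to reproduce here. The check is the overlap between the recall window and the trial calendar.

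**Inputs**
- Recall length L: three months (Quality of Life), taken as 12 or 13 weeks to show the range.
- MIDAS visits t: weeks 0, 4, 8, 12, 16 and 20 (Table 1).
- Treatment from week 0 to week 8 (Study Design and Table 1).

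**Pre-treatment share of the window**

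The window at week t runs from t − L to t. Its pre-treatment share is max(0, L − t) / L. This is also the share of the window already scored at week 0.

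**Share of an effect captured**

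Suppose disability accrues at d per week before treatment and d − e per week from week 0 on, with all recalled weeks counted equally.
- Score at week 0: L·d.
- Score at week t ≤ L: (L − t)·d + t·(d − e) = L·d − t·e.
- Change: t·e in size, against L·e for a window wholly after week 0.
- Captured share: min(t, L) / L.

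The same factor multiplies the between-arm difference, because each arm's change is t times its own e.

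| Week | Pre-treatment share, L = 12 | Pre-treatment share, L = 13 | Captured share, L = 12 | Captured share, L = 13 |
|---|---|---|---|---|
| 4 | 8/12 = 67% | 9/13 = 69% | 33% | 31% |
| 8 | 4/12 = 33% | 5/13 = 38% | 67% | 62% |
| 12 | 0/12 = 0% | 1/13 = 8% | 100% | 92% |
| 16 | 0% | 0% | 100% | 100% |
| 20 | 0% | 0% | 100% | 100% |

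Under these assumptions an unchanging effect would show on MIDAS as a rise from about one third of its size at week 4 to between 92% and 100% at week 12. That is a time course produced by the window alone.

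**What the later windows contain**
- Week 12: all 8 treatment weeks, 4 follow-up weeks and at most one pre-treatment week.
- Week 16: 4 of 12 (33%) or 5 of 13 (38%) treatment weeks, the rest follow-up.
- Week 20: 0 of 12 or 1 of 13 treatment weeks, the rest follow-up.

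**If the recall were 4 weeks**

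With L = 4 the pre-treatment share is zero at every post-baseline visit, and the problem disappears.

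**The case against.** The case for leaving the plan alone has real substance.

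- **Limited reach.** MIDAS is one of two quality-of-life scales within one of several secondary endpoints. The primary diary outcomes are untouched, MSQ is collected at the same visits, and three of the five post-baseline MIDAS visits are clean or nearly so. This stands.
- **Direction.** The dilution pulls both arms' changes, and their difference, toward zero. It favours neither arm and does not by itself produce a spurious difference. This stands.
- **A null is not thereby explained.** A reader might infer that a null MIDAS result at week 8 would be an artefact of the recall window. The documents do not support that. Week 8 still captures about 62–67% of a constant effect. The article itself allows that the two acupuncturists may perform alike, and it lists an underestimated sample size as a limitation. The window is one possible contributor.
- **The percentages are illustrative.** They depend on even accrual, equal recall weighting and a full effect from week 0. A gradual onset would lower the captured share at weeks 4 and 8. This stands, so the figures are given as ranges with their assumptions.
- **Overlap between successive windows.** Consecutive MIDAS windows share 8 of 12 or 9 of 13 weeks. A reader might infer that this invalidates the analysis. Statistical Analysis names between-group tests and no visit-to-visit MIDAS comparison, so no harm is shown.
- **Left to the analysis plan.** Which visits to emphasise is often settled there, and an adapted MIDAS form may exist. But the article itself states the recall, the interval and the change measure, and as stated they do not fit together. It gives a 4-week recall for the anxiety and depression scales and a three-month one for MIDAS. This objection does not remove the point.

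**Conclusion.** The point holds for weeks 4 and 8. As written, MIDAS change at week 4 mostly re-measures pre-treatment time and at week 8 partly does. Under the stated assumptions, roughly two thirds of a true effect or between-arm difference is lost at week 4 and about one third (33–38%) at week 8. A null at those visits could partly reflect the recall window, and an apparent build-up from week 4 to week 12 could be partly mechanical.

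The point does not extend to weeks 16 and 20, and it touches week 12 by at most about one week. It is worth correcting because week 8 is the end of treatment and the correction is cheap, but it does not threaten the trial's main conclusion.

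**What to change.** Choose one of two edits.

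1. **If MIDAS keeps its three-month recall:** base the between-group analysis of MIDAS change on visits whose window lies after week 0. These are weeks 16 and 20. Week 12 is usable with a note that its window may hold about one pre-treatment week; it is also the window that contains the whole treatment phase. Make weeks 4 and 8 descriptive, or remove them from Table 1. Use MSQ for the 4-weekly course and the end-of-treatment quality-of-life comparison. When reporting weeks 16 and 20, say that those windows are mainly follow-up.
2. **If a 4-week recall version is used at every visit, baseline included:** correct the Quality of Life paragraph to say so. The 4-weekly change scores can then stand.

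Either is an edit to the text and, at most, the schedule and analysis; no new data are needed. Dropping weeks 4 and 8 would also shorten those visits for patients. The cost of the first option is that there is no inferential MIDAS result at the end of treatment.
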